| Secondary Efficacy Endpoints                                                                    | 
 
Absolute change in Nurick score from admission to 180 days
 
Absolute change in SF-36v2.0™ PCS from baseline to 180 days
 
Absolute change in Neck Disability Index (NDI) from baseline to 180 days
 
Absolute change in Cervical Pain Numeric Rating Scale from baseline to 180 days
 
Absolute change in EQ-5D utility score from baseline to 180 days
 
Absolute change in ASIA Motor score from baseline to 180 days
 
Absolute change in ASIA Sensory score from baseline to 180 day
 
Absolute change in Grip score from baseline to 180 days
 
Rate of neurological complications
 
                                                                                                                                                                                                                              |
| Estimated Enrollment                                                                            | 270 subjects randomized 1:1 to riluzole and placebo                                                                                                                                                                                                                                                                                                                                                                                                                                                                                                                                                                                                                                                                                                                                                                                                                                                                             |

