### 3.3 Study Scope and Duration

---

This is a multi-center, prospective, double-blinded, randomized placebo-controlled clinical trial to evaluate if sodium-glutamate antagonist riluzole in a dose of 50mg BID 14 days before the surgery and continuing for 28 days after the surgery is superior to placebo in patients with moderate and severe cervical spondylotic myelopathy undergoing surgical decompression.

The study will involve up to 16 investigational sites and enroll 270 evaluable subjects. A randomization ratio of one riluzole subject to one placebo control subject (1:1) will be utilized. The sample size may change during the interim analysis due to adaptive statistical design.

Patients scheduled for elective surgical decompression due to cervical spondylotic myelopathy will be screened for inclusion in the study. If the patient meets all of the eligibility criteria, he/she will be enrolled and randomized to either the riluzole or placebo controlled group. The randomization will occur 14-17 days prior to surgery. Subjects will begin receiving study medications 14 days prior to the planned surgery date and continue receiving it for 28 days following the surgery. The riluzole group will receive riluzole in a dose of 50 mg every 12 hours. The control group will receive placebo capsules that are the same color, size, taste and

Efficacy of Riluzole in Patients with Cervical Spondylotic Myelopathy Undergoing Surgical Treatment. A Randomized, Double-Blind, Placebo-Controlled, Multi-Center Study

consistency as riluzole capsules but will not have the active ingredient. Subjects, investigators, and study research personnel will be blinded to the randomization code. The study Contract Research Organization (CRO) will maintain randomization and blinding. Treatment allocation will be un-blinded for the purpose of interim analysis. The results of the interim analysis and the un-blinded data will not be shared with investigators, subjects or those involved in the execution of the study.

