##### 4.6.2 Enrolled Subject

A subject is considered to be enrolled when the randomization occurs.

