## 5.7 Sample Size Estimate

---

The required sample size is 270 evaluable subjects, or 135 subjects per study arm. The rationale for the sample size is as follows.

Sample size has been calculated to provide 80% power in testing the primary superiority hypothesis. The estimate has been made by the sample size estimation software package East v5.3 (Cytel, Inc.).

Using the data from the performed CSM study (data on file with the Sponsor), the following empirical estimates have been obtained for the primary outcome parameters.

| Endpoint              | N   | Mean | Standard Deviation |
|-----------------------|-----|------|--------------------|
| $\Delta mJOA_{180-b}$ | 146 | 2.81 | 2.57               |

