**Table 3 Sample size estimate  $\Delta mJOA_{180-b}$**

| Plan ID                                           | Parameter          |
|---------------------------------------------------|--------------------|
| Type of the hypothesis                            | 1-Sided            |
| Type I Error ( $\alpha$ )                         | 0.025              |
| Power ( $1 - \beta$ )                             | 0.80               |
| Randomization Ratio (Investigational vs. Control) | 1:1                |
| Planned Number of Interim Looks                   | 2                  |
| Spacing of Looks                                  | 65%, 100%          |
| Hypothesis to be Rejected                         | H0 or H1 (binding) |
| Boundary Family                                   | Published Function |
| Boundary to Reject H0                             | O'Brien-Fleming    |
| Boundary to Reject H1                             | Gamma (-2)         |
| Difference of Means Assuming $H_1$                | 0.9                |
| Standard Deviation ( $\sigma$ )                   | 2.57               |
| Sample Size                                       | 270 (135 per arm)  |

Under the above assumptions, the estimated sample size is 270 evaluable subjects. (135 in the riluzole arm and 135 in the control arm). In order to account for loss of power due to loss of follow-up and possible adjustments for baseline factors we will increase sample size for 10% to **300 enrolled** subjects.

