**Figure 1 Rejection boundaries for mJOA**

[figure not shown]

Table 4 shows simulation results of the testing under the assumption of no difference between the investigational and control groups. The simulation shows that under those conditions, the H1 will be rejected in 82.5% of the cases at the interim analysis (futility stop) and at 97.64% cases at the final analysis.

Table 5 shows simulation results of the testing under the assumption of a treatment effect of the size of 1 absolute point in mJOA, the background for the sample size estimate. The simulation shows that under those conditions, the H0 will be rejected in 40.95% of the cases at the first interim analysis, and in cumulative 80.05% at the last analysis.

Efficacy of Riluzole in Patients with Cervical Spondylotic Myelopathy Undergoing Surgical Treatment. A Multi-Center Double Blind Randomized Controlled Study.

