**Table 5. Simulation results: difference between investigational and control group is 0.9 absolute points in mJOA**

[figure not shown]

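### The synopsis sets 270 randomised where section 5.7 sets 300 enrolled to yield 270 evaluable; separately, section 5.8 labels as a 1-point effect the power computed at 0.9

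*Protocol*

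**What the plan says.** **Number of subjects.** The synopsis, under Estimated Enrollment, states "270 subjects randomized 1:1 to riluzole and placebo". Section 3.3 says "The study will involve up to 16 investigational sites and enroll 270 evaluable subjects". Section 5.7 opens with "The required sample size is 270 evaluable subjects, or 135 subjects per study arm". After Table 3 it repeats "Under the above assumptions, the estimated sample size is 270 evaluable subjects" and adds an allowance for loss to follow-up and possible baseline adjustment: "we will increase sample size for 10% to 300 enrolled subjects".

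Two other provisions fix what these numbers mean. Section 4.6.2 states "A subject is considered to be enrolled when the randomization occurs", and section 4.5.3 says the same. Section 4.6.3 says that subjects who withdraw, or whom the investigator withdraws, are not replaced.

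**Effect size.** Table 3 gives a difference of means of 0.9 under the alternative, with SD 2.57, one-sided alpha 0.025, 80% power and looks at 65% and 100%. The plan details in Table 4 also list 0.9 as the design difference. The title of Table 5 reads "difference between investigational and control group is 0.9 absolute points in mJOA". The text of section 5.8, describing Table 5, says the simulation was run "under the assumption of a treatment effect of the size of 1 absolute point in mJOA, the background for the sample size estimate", and reports rejection of the null in 40.95% of cases at the interim and 80.05% overall.

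**The concern.** Because enrolled means randomised in this protocol, 270 randomised (synopsis) and 300 enrolled (section 5.7) cannot both be the target. The synopsis is where many readers look for that number. If recruitment stops there, any loss of 180-day data takes the evaluable number below the 270 on which 5.7 bases its 80% power, and nothing in the withdrawal rules makes up the difference.

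The effect-size sentence is a separate slip. A reader who relies on the text of 5.8 would believe that the trial was sized for 1 mJOA point with 80% power. The design tables say it was sized for 0.9.

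**Working it through.** **Inputs.** Difference 0.9, SD 2.57, one-sided alpha 0.025, 1:1 allocation and looks at 65% and 100% (Table 3). Boundaries on the Z scale as printed in Table 4: interim efficacy 2.5469, interim futility 0.9365, final 1.9896. Sample sizes at the looks, also from Table 4: 175.26 and 269.64.

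**Formulas.** With total evaluable n split 1:1, the test statistic has mean δ / (σ·√(4/n)). The correlation between the two looks is √0.65. Interim rejection is P(Z1 > 2.5469). Overall power adds P(0.9365 < Z1 < 2.5469 and Z2 > 1.9896), obtained by numerical integration. The futility boundary is treated as followed.

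**Step 1: reproduce the plan at δ = 0.9.**
- Mean of Z1 = 0.9 / (2.57·√(4/175.26)) = 2.318; mean of Z2 = 0.9 / (2.57·√(4/269.64)) = 2.875.
- Interim rejection 40.95%; overall power 80.0%.
- Solving for the maximum sample size that gives 80% power returns 269.6, with the same three boundaries as Table 4.

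So 270 evaluable subjects, 40.95% and 80.05% (a simulated value) all belong to 0.9.

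**Step 2: same design at δ = 1.0.**
- Mean of Z1 = 2.576; mean of Z2 = 3.195.
- Interim rejection 51.1%; overall power 87.6%.
- A trial sized for 80% power at 1 point would need a maximum of about 218 evaluable subjects, not 270.

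**Step 3: enrolment.** 270 / (1 − 0.10) = 300, the figure in 5.7. (Multiplying instead, 270 × 1.10 = 297, which also rounds to 300.) The step from 270 evaluable to 300 enrolled is correct.

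**Step 4: power at δ = 0.9 if only 270 are randomised.** The interim stays at 65% of the reduced total and the boundaries are unchanged.

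| Loss of 180-day data | Evaluable | Power |
|---|---|---|
| none | 270 | 80% |
| 5% | 270 × 0.95 ≈ 256 | 77.9% |
| 10% | 270 × 0.90 = 243 | 75.8% |

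**The case against.** The sample-size calculation is not faulty. In section 5.7 the values 0.9, 2.57, 80%, 270 evaluable and 300 enrolled agree with one another, and 5.7 is the detailed statement. The synopsis line is headed as an estimate, and section 3.3 allows the sample size to change at the interim. All of this is true and limits the practical risk. It does not reconcile the two totals: a possible later change presupposes one starting number, and the protocol gives two.

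A reader might infer that the synopsis figure costs the trial a definite four points of power. The document does not support that. Section 5.7 assigns the 10% jointly to loss to follow-up and baseline adjustment, without a split, so 75.8% is the low end of a range. The primary analysis is also on the ITT population with imputed 6-month values (sections 5.10.1 and 5.10.5), so the analysed number would not simply be 243. Imputation does not, however, restore the information in missing scores, and 5.7 sizes the trial on evaluable subjects.

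A reader might also infer from section 5.8 that the trial is underpowered. The reverse holds: if the true effect were 1 point, power at 270 evaluable would exceed the stated 80%. Nor do the documents show that the mislabelled 1 point would carry into the sample-size readjustment in section 5.9. That section leaves the method to the SAP, and nothing indicates that the sentence in 5.8, rather than the 0.9 design input, would be used.

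Finally, section 3.3's wording is compatible with 5.7. It counts evaluable subjects and omits the 300, so it needs clarifying rather than correcting.

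**Conclusion.** Both contradictions stand in the current text, and they are independent of each other.

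The more important one is the enrolment total: 270 randomised against 300 enrolled, a difference of 30 subjects for the same quantity. Recruiting only to the synopsis figure gives power at 0.9 between about 76% and 80%. This assumes SD 2.57, the Table 4 boundaries, the interim at 65% of the evaluable total, and a loss of 180-day data between 10% and none.

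The second is a wrong label. The 40.95% and 80.05% in section 5.8 are results for 0.9, not for 1 point, which would give about 51% and 88%. It misstates the effect the trial was sized for and changes no design number.

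Both should be corrected; neither calls for a new sample-size calculation.

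**What to change.** - **Synopsis, Estimated Enrollment:** state 300 subjects randomised 1:1, to give 270 evaluable.
- **Section 3.3:** state that 300 subjects will be enrolled to obtain 270 evaluable.
- **Section 5.8, sentence on Table 5:** replace the 1-point effect with 0.9 points, as in Table 3 and the Table 5 title.

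The cost is wording only. Section 5.7 already contains 300, Tables 3 and 5 already contain 0.9, and the design and its boundaries stay as they are.

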### 3 Background Information

---

#### 3.1 Justification for Investigation

---

CSM (cervical spondylotic myelopathy) is the most common cause of spinal cord impairment worldwide. The pathophysiology of CSM involves static and dynamic compression of spinal cord which triggers ischemia and secondary cell death by a variety of mechanisms, which prominently include sodium influx and glutamatergic excitotoxicity. While there is emerging evidence from the recently completed AOSpineNA prospective study that surgical decompression is an effective treatment for CSM, it is clear that many patients have substantial residual neurological impairment. Moreover, while surgery is relatively safe, approximately 3% of patients sustain a neurological complication, of which C5 root palsy is the most common adverse outcome. Given this background and compelling evidence from preclinical models of nontraumatic and traumatic spinal cord injury (SCI), there is a strong rationale to consider the potential benefit of adding a neuroprotective drug which targets sodium/glutamate excitotoxicity to the treatment of patients with CSM undergoing surgical decompression. Riluzole, a potent sodium/glutamate antagonist has been widely studied in many models of neurotrauma and neurodegenerative disease. This drug is FDA-approved for the treatment of amyotrophic lateral sclerosis, which has some similar clinical features to CSM. Moreover, riluzole is currently under investigation for traumatic SCI. Given this background, there is a strong rationale to consider studying the potential neurological benefits of riluzole as an adjunctive treatment to surgical decompression in patients with CSM.

#### 3.2 Riluzole

---

Riluzole tablets, a capsule-shaped, white, film-coated tablet for oral administration containing 50 mg of riluzole. Chemically it is 2-amino-6-(trifluoromethoxy)benzothiazole. Its molecular formula is  $C_8H_5F_3N_2OS$  and its molecular weight is 234.2. Its structural formula is as follows:

[figure not shown]

Riluzole, a benzothiazole anticonvulsant  $Na^+$  channel blocker, has been shown in two randomized controlled trials to promote increased survival and attenuate neurological dysfunction in patients with amyotrophic lateral sclerosis (ALS), a progressive neurodegenerative disorder characterized by motoneuron and corticospinal tract degeneration (Lacomblez et al., 1996, Hugon, 1996, Bensimon et al., 1994b). A recent Cochrane review has confirmed that the evidence for safety and efficacy in this clinical scenario is persuasive (Miller et al., 2007).

## Efficacy of Riluzole in Patients with Cervical Spondylotic Myelopathy Undergoing Surgical Treatment. A Randomized, Double-Blind, Placebo-Controlled, Multi-Center Study

Given the data in the setting of ALS, it is not surprising that riluzole has been examined in other disease models characterized by sodium and glutamate toxicity. Several studies from a number of independent laboratories, in various species of animals, have shown that riluzole is neuroprotective and promotes functional neurological recovery in models of brain and spinal cord ischemic and traumatic injury (Heurteaux et al., 2006, Ates et al., 2007, Lang-Lazdunski et al., 1999, Schwartz and Fehlings, 2001). Other authors have found that the effects of riluzole are synergistic with the effects of methylprednisolone, which is the only drug used in routine clinical practices to attenuate secondary injury effects after SCI (Mu et al., 2000). In a recent study of prolonged administration of riluzole in Huntington's disease, no benefit was found in slowing disease progression, but riluzole was well-tolerated. Adverse effects were virtually similar in 357 subjects treated with riluzole, compared to 180 placebo subjects. Thirteen subjects had elevated liver enzymes and lead to five subjects discontinuing treatment. (Landwehrmeyer et al., 2007).

Riluzole exerts neuroprotective properties in the injured cord following systemic administration by sparing gray and white matter in rostro-caudal regions surrounding the injury epicenter (Schwartz and Fehlings, 2001). In addition to its ability to antagonize Na+ channels, riluzole is also known to inhibit presynaptic Ca2+-dependent glutamate release (Wang et al., 2004). However, given the lack of synaptic connections within white matter, the axon sparing property attributed to riluzole can likely be assigned to its ability to decrease the levels of [Na+]i and intracellular calcium [Ca2+]i.

The use of riluzole as a therapy for SCI is potentially feasible, as it has already received approval from the Food and Drug Administration (FDA) for treatment of amyotrophic lateral sclerosis (ALS) (Miller et al., 2007) at a dose of 100 mg/day. Notably, riluzole is without potent neurotoxic and cardiotoxic adverse effects (Bensimon et al., 1994a), although potential hepatotoxicity has been noted (Bensimon and Doble, 2004). While riluzole is administered for the lifetime of the patient with ALS, it would appear that the duration of therapy in the setting of spinal cord injury would not need to exceed 14 days, based on preclinical animal models and given the anticipated duration of sodium and glutamate mediated secondary injury (Schwartz and Fehlings, 2001, Park et al., 2004).

### 3.2.1 Pharmacology of Riluzole

---

In human studies, riluzole has been administered orally in a dose of 50 mg BID. The half-life of riluzole is 12 hours. Most drugs reach steady state plasma concentrations in 4-5 half lives and the same is assumed for riluzole. Riluzole is highly bound to plasma proteins – 97.5%, like phenytoin. In subjects taking other drugs that bind to plasma proteins the binding sites compete and presumably result in more free riluzole in the plasma with greater drug activity. Riluzole is metabolized in the liver by an enzyme of the cytochrome P (CYP) 450 family. There are multiple CYP genes; however, most of the drugs metabolizing enzymes are in the CYP 1, 2 & 3 families. Riluzole is specifically metabolized by a member of the CYP 1A2 subfamily whose substrates include acetaminophen, caffeine and warfarin. Other drugs that are metabolized by CYP 1A2 are Tacrine (Cognex), Omeprazole (Prilosec) and quinolone antibiotics and theophylline. Co-administration of riluzole and these drugs can increase riluzole blood concentration.

### 3.2.2 Regulatory Status

---

## Efficacy of Riluzole in Patients with Cervical Spondylotic Myelopathy Undergoing Surgical Treatment. A Randomized, Double-Blind, Placebo-Controlled, Multi-Center Study

Riluzole is approved by FDA and Health Canada for treatment of amyotrophic lateral sclerosis. It is not approved by the FDA or by Health Canada for treating patients undergoing cervical surgical decompression for cervical spondylotic myelopathy.

The IND regulations [21 CFR 312.2(b)] state that clinical investigation of a drug product that is lawfully marketed in the United States is exempt from the requirements for an IND if all of the following apply: 1. The investigation is not intended to be reported to FDA as a well-controlled study in support of a new indication for use, nor intended to be used to support any other significant change in the labeling for the drug.; 2. The investigation is not intended to support a significant change in the advertising for a prescription drug product.; 3. The investigation does not involve a change in route of administration, dosage level, or patient population, or other factor that significantly increases the risks (or decreases the acceptability of risks) associated with use of the drug product.; 4. The investigation is conducted in compliance with the requirements for institutional review (21 CFR Part 56) and informed consent (21 CFR Part 50); 5. The investigation is conducted in compliance with the requirements of 21 CFR 312.7, i.e., the drug may not be represented as safe or effective for the purposes for which it is under investigation, nor may it be commercially distributed or sold. In addition, 21 CFR 312.2(b)(5) states a clinical investigation involving the use of a placebo is exempt from the IND requirements if the investigation does not otherwise require submission of an IND.

The FDA has been contacted by the Sponsor requesting clarification as to whether the trial meets the above requirements for IND exemption. The Sponsor has received a letter from the FDA stating that they acknowledge receipt of the IND Application and after review, it has been determined that the trial meets all of the requirements for exemption and therefore an IND is not required to conduct the investigation in accordance with 21 CFR 312.2(b)(4)

Health Canada regulates investigator-driven research in the same way as industry-sponsored research. The "No Objection Letter" (equivalent to US FDA IND approval) will be obtained from Health Canada prior to beginning the study at Canadian sites.

### 3.3 Study Scope and Duration

---

This is a multi-center, prospective, double-blinded, randomized placebo-controlled clinical trial to evaluate if sodium-glutamate antagonist riluzole in a dose of 50mg BID 14 days before the surgery and continuing for 28 days after the surgery is superior to placebo in patients with moderate and severe cervical spondylotic myelopathy undergoing surgical decompression.

The study will involve up to 16 investigational sites and enroll 270 evaluable subjects. A randomization ratio of one riluzole subject to one placebo control subject (1:1) will be utilized. The sample size may change during the interim analysis due to adaptive statistical design.

Patients scheduled for elective surgical decompression due to cervical spondylotic myelopathy will be screened for inclusion in the study. If the patient meets all of the eligibility criteria, he/she will be enrolled and randomized to either the riluzole or placebo controlled group. The randomization will occur 14-17 days prior to surgery. Subjects will begin receiving study medications 14 days prior to the planned surgery date and continue receiving it for 28 days following the surgery. The riluzole group will receive riluzole in a dose of 50 mg every 12 hours. The control group will receive placebo capsules that are the same color, size, taste and

Efficacy of Riluzole in Patients with Cervical Spondylotic Myelopathy Undergoing Surgical Treatment. A Randomized, Double-Blind, Placebo-Controlled, Multi-Center Study

consistency as riluzole capsules but will not have the active ingredient. Subjects, investigators, and study research personnel will be blinded to the randomization code. The study Contract Research Organization (CRO) will maintain randomization and blinding. Treatment allocation will be un-blinded for the purpose of interim analysis. The results of the interim analysis and the un-blinded data will not be shared with investigators, subjects or those involved in the execution of the study.

Subjects will be evaluated according to the schedule set forth in this clinical protocol. The schedule includes an evaluation at 14 days before the surgery (- 14 days), admission, surgery (Day 0), post-surgery, a postoperative discharge exam, 35 days, 180 days and 365 days. The 365-day follow-up will be performed until the last subject enrolled and still active in the study (i.e. not withdrawn) has completed the 180-day follow-up. The enrollment period is expected to be approximately 24 months and subjects will be followed for 6 months for the evaluation of the primary efficacy endpoint. The study duration is approximately 30 months.

